### Outcomes

#### Primary outcome

Primary outcome is the post-treatment assessment with the HRSD [31]. The HRSD is a standardised clinical interview developed to assess severity of depressive symptoms. The researcher conducting the interviews is trained in the procedure and blinded with regard to the treatment group.

#### Secondary outcomes

Secondary outcomes will be conducted post-treatment by using the following measures. The Hamilton Depression Rating Scale (HAM-D6) is a six-item self-report rating scale (corresponding to the 17-item observer-rated HRSD), which measures the core symptoms of the depression construct on a unipolar scale. The HAM-D6 questionnaire has been shown to be a reliable and valid measure of the severity of depressive symptoms in a clinical sample [32]. The Behavioural Activation for Depression Scale (BADS) is a 25-item questionnaire measuring changes in avoidance and activation over the course of behavioural activation and has been shown to be reliable and valid in a community sample with elevated depressive symptoms [33]. The Penn State Worry Questionnaire (PSWQ) is a 16-item questionnaire assessing the general trait of worry and has been shown to be reliable and valid in a clinical sample [34]. The Rumination Response Scale (RRS) is a 22-item self-report measure that assesses ruminative response to depressive symptoms. Participants are asked to indicate the frequency of rumination with the total score indicating the severity of rumination used as a strategy in response to depressive symptoms [35]. The Generalised Anxiety Scale (GAD-7) is a seven-item questionnaire assessing the severity of symptoms of generalised anxiety disorder. GAD-7 has been shown to be valid in a community sample [36]. The World Health Organization Well Being Index (WHO-5) is a five-item questionnaire assessing the level of well-being [37]. The Trail Making Task A and B is a neuropsychological test of visual attention and task switching. It consists of two parts in which the test respondent is asked to connect 25 dots as fast as possible while still maintaining accuracy [38]. The Dot Probe Task is a non-verbal computerized task assessing the level of visual attentional bias from emotional pictures [39]. Furthermore, assessment with Dot Probe Task, HAM-D6, RSS, PSWQ, and BADS will take place after the fourth and the eighth sessions. A 6-month post-treatment follow-up will be conducted to measure the level of depressive symptoms with HRSD, and depressive relapse will be assessed by a diagnostic interview based on DSM-IV criteria for depression.

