## Background

Cognitive behavioural therapy (CBT) is a recommended treatment for unipolar depression, and a large number of studies provide supportive evidence for its efficacy in both an individual as well as a group format [1–3]. CBT has been shown to be effective in the short term and to have enduring effects in reducing the risk of returning symptoms after treatment has ended. However, approximately one third of the patients do not respond satisfactorily to the treatment [4, 5], and post-treatment residual symptoms are a common problem; as many as 30–50 % of remitted patients experience residual symptoms at the end of treatment [6]. Residual symptoms of depression are associated with ongoing psychosocial and functional disability and have been demonstrated to predict poorer long-term outcome of major depression, including increased rates of relapse [7–9]. A recent meta-analysis reports relapse rates of around 29 % within 1 year and 56 % within 2 years [10].

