Recent studies have evaluated the potential benefit of continuation-phase CBT in reducing residual symptoms as well as in preventing subsequent depressive relapse or recurrence. In general, continuation-phase cognitive therapies have proven to be beneficial in reducing rates of relapse and recurrence [10]. Yet, in most of these studies, only a modest reduction in residual symptoms was observable [11, 12], indicating the possibility of further improvement in efficacy by targeting key residual symptoms. With the aim of improving efficacy, an increased focus has been directed toward a common residual symptom, namely depressive rumination [13, 14]. Rumination is a passive process of recurrent negative thinking and dwelling on negative affect, causes, and symptoms [15] and has been shown to be a major factor in vulnerability to depression as well as predicting the onset, severity, and duration of future depressive episodes [16, 17]. Consequently, if involved in the pathogenesis of depression, rumination may constitute a relevant target for psychological intervention. In support of this, recent psychotherapeutic interventions designed to target depressive rumination show promising results [18–20]. The strongest evidence thus far exists for the rumination-focused cognitive behavioural therapy (RFCBT) developed by Watkins and colleagues [18]. RFCBT is based on a conceptualization of repetitive thinking that differentiates between a functional and a dysfunctional style of thinking. The helpful style is characterized by being concrete and specific, whereas the unhelpful style is abstract and evaluative and does not lead to problem solving (rumination) [21]. In RFCBT, rumination is formulated as a habitual behaviour controlled by the laws of behavioural psychology [22] and maintained by negative reinforcement. Rumination can act as a form of avoidance by thinking about difficulties rather than confronting them directly in the real world and thereby avoiding the risk of failure and negative outcomes. Hence, rumination can become reinforced by escape and avoidance. Grounded in behavioural psychology and research, RFCBT focuses on functional analyses of the target behaviour, rumination, and combines strategies from behavioural activation with novel strategies to foster concrete, process-focused, and specific thinking. RFCBT differs from standard CBT by focusing on modifying the process of thinking, whereas CBT focuses on modifying the content of the thoughts and content of dysfunctional schemas [14]. With only a handful of trials conducted, the evidence for RFCBT is still sparse, although it is promising. For example, in a recent clinical trial with patients with medication-refractory residual depression, 42 patients were randomly allocated (1:1) to treatment-as-usual (TAU) consisting of continuation anti-depressants and outpatient clinical management or to TAU plus up to 12 sessions of individual RFCBT. RFCBT was found to be superior to TAU; 62 % of patients in the RFCBT treatment condition achieved remission, compared with 21 % in the TAU [18]. However, to date, no study has made a direct comparison of RFCBT with standard CBT. The aim of the present study is to compare group-based rumination-focused cognitive behaviour therapy (g-RFCBT) with group-based standard cognitive behavioural therapy (g-CBT) for depression on the effectiveness of treatment and the reduction of relapse rates at 6-month follow-up.

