
## Methods/design

This study is a two-arm pragmatic randomised controlled trial comparing the effectiveness of g-RFCBT with the effectiveness of g-CBT for treatment of depression. Our primary hypothesis is that g-RFCBT will be superior to g-CBT in reducing depressive symptoms measured on the score on the Hamilton Rating Scale for Depression (HRSD) at the end of treatment. Our secondary hypothesis is that g-RFCBT will be superior to g-CBT in reducing relapse at 6-month follow-up after the end of treatment. Relapse is defined as a score of 13 points or more on the HRSD.

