### Eligibility criteria

Patients who are between 18 and 65 years of age and who meet Diagnostic and Statistical Manual of Mental Disorders, 4th Edition (DSM-IV) criteria for a current episode of unipolar major depression or recurrent or chronic depression in a structured M.I.N.I. 5.0 interview and with a score of 13 or more on the 17-item HRSD can be included [18]. Patients with psychotic symptoms, bipolar disorder, functional illiteracy, or alcohol and drug abuse will be excluded. Patients with depression and co-morbid anxiety or personality disorder are included in the study. Patients receiving anti-depressants will not be excluded.

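### Relapse defined as HRSD of 13 or more is status at a single visit, requires no prior remission, and is not reconciled with the DSM-IV interview also planned for relapse

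*Protocol article*

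**What the plan says.** The protocol article describes relapse in four places.

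- **Background** gives the aim as comparing effectiveness and "the reduction of relapse rates at 6-month follow-up".
- **Methods/design** turns this into a hypothesis: "Our secondary hypothesis is that g-RFCBT will be superior to g-CBT in reducing relapse at 6-month follow-up after the end of treatment". The next sentence is the only explicit definition: "Relapse is defined as a score of 13 points or more on the HRSD". It gives no time window and does not require the patient to have remitted or responded first.
- **Eligibility criteria** uses the same cut-off for entry: patients "with a score of 13 or more on the 17-item HRSD can be included".
- **Secondary outcomes** schedules one visit after the end of treatment: "A 6-month post-treatment follow-up will be conducted to measure the level of depressive symptoms with HRSD". The same sentence continues that "depressive relapse will be assessed by a diagnostic interview based on DSM-IV criteria for depression". It does not state what period the interview covers.

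No assessment is described between end of treatment and 6 months. The interim measurements ("assessment with Dot Probe Task, HAM-D6, RSS, PSWQ, and BADS will take place after the fourth and the eighth sessions") fall during treatment and do not include the HRSD. Randomisation and concealment says that all assessments are made by researchers blind to allocation.

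**The concern.** Relapse is an event over time: a patient gets better and then becomes depressed again. The Methods/design definition does not capture this, for two reasons that work in opposite directions.

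1. **Missed events.** A patient who relapses in month 2 and scores below 13 at month 6 is counted as relapse-free. The outcome then mixes the onset of relapse with how long episodes last and with any treatment given after relapse. Antidepressant use is unrestricted under Interventions.
2. **False events.** A patient who enters at 13 or more, never falls below it, and is still there at 6 months is counted as relapsed. That is non-response, which the primary outcome already measures.

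The DSM-IV interview could avoid both problems, but the article does not say whether it covers the interval or whether it replaces the HRSD definition. Two analysts could therefore follow the article faithfully and report different relapse rates for the same patients. This matters because relapse carries a named hypothesis and is part of the stated aim.

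**Working it through.** **The plan's own figures.** The article gives no event rate, power or sample size for relapse. Its sample size rests on HRSD change alone: (7.81 − 3.52)/6 = 0.715, stated as 0.7, which gives 44 per arm by a two-sample t-test (43.9) and 44/0.8 = 55 after 20 % dropout. These figures reproduce, but they say nothing about relapse. What follows is an illustration, not a correction of a stated number.

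**The two definitions side by side**

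| | Methods/design | Secondary outcomes |
|---|---|---|
| Instrument | HRSD of 13 or more | DSM-IV diagnostic interview |
| When taken | Only HRSD after end of treatment is at 6 months | 6-month visit |
| Period covered | Status at the visit | Not stated |
| Prior remission required | No | Not stated |
| Tests the secondary hypothesis | Implied by position | Not stated |

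**Missed events under a status reading**

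Input from the document: about 29 % relapse within 1 year (Background). Assumptions: constant hazard, everyone well at end of treatment, exponential episode length with mean D months, first relapse only. The documents give no D, so a range is shown.

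- Monthly hazard: h = −ln(1 − 0.29)/12 = 0.3425/12 = 0.02854.
- Cumulative relapse by 6 months: 1 − exp(−6h) = 1 − 0.8426 = 15.7 %.
- Still in episode at the visit: the integral from 0 to 6 of h·exp(−ht)·exp(−(6 − t)/D) dt = [h/(1/D − h)]·[exp(−6h) − exp(−6/D)].

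| Mean episode D | Calculation | Visible at visit | Share missed |
|---|---|---|---|
| 3 months | 0.0936 × (0.8426 − 0.1353) | 6.6 % | 58 % |
| 4 months | 0.1289 × (0.8426 − 0.2231) | 8.0 % | 49 % |
| 6 months | 0.2066 × (0.8426 − 0.3679) | 9.8 % | 38 % |
| 12 months | 0.5209 × (0.8426 − 0.6065) | 12.3 % | 22 % |

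A simpler model with onset uniform over the 6 months gives nearly the same shares missed: 57 %, 48 %, 37 % and 21 %.

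With 64 per arm, an assumed halving of risk, uniform onset, and no allowance for clustering or dropout, power is about 28 % on the cumulative rate. On status at the visit it is about 14 % (D = 3) or 19 % (D = 6). Power is low either way, and a status reading lowers it further.

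**False events under the HRSD definition**

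Let u be the share of patients at 13 or more at both end of treatment and 6 months. The counted rate is u + (1 − u) × (visible rate). The documents give no u. Background says roughly one third of patients do not respond satisfactorily to CBT. Taking u = 1/3 purely as an assumption (non-response is not the same thing as a score of 13 or more):

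- D = 3: 0.333 + 0.667 × 0.066 = 37.7 %, of which 0.333/0.377 = 88 % never improved.
- D = 12: 0.333 + 0.667 × 0.123 = 41.5 %, of which 0.333/0.415 = 80 % never improved.

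On the same assumption, true cumulative relapse among all patients would be 0.667 × 15.7 % = 10.5 %. The second error can therefore be larger than the first and of opposite sign.

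**The case against.** The strongest reply is that Secondary outcomes already separates the two jobs: the HRSD measures symptom level and the diagnostic interview assesses relapse. One visit does not imply a one-day reference period, since an interview can ask about the whole interval. A condensed article may leave the look-back to the full protocol. This stands in part. A reader might infer that interval relapses are missed whichever definition is used, and that the hypothesis is certainly tested on point prevalence. The article does not support that for the interview, because it is silent on the period covered. It does not dispose of the point, however. The HRSD rule is stated in the article directly after the hypothesis, and nothing there says that the interview supersedes it.

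A second reply is that the hypothesis is worded as relapse at 6-month follow-up, which permits status at the visit. That is a possible estimand, but it is current depression, and a definition that also counts patients who never remitted does not measure relapse under either reading.

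A third reply concerns the figures in "A recent meta-analysis reports relapse rates of around 29 % within 1 year and 56 % within 2 years". A reader might take these as the benchmark against which the trial will be judged. They are background only; no section uses them for planning or comparison. They serve here solely as an input to an illustration.

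Finally, a reader might infer that the trial loses a large share of its relapse events, or that a spurious benefit is to be expected if episodes are shorter in one arm. Neither is established. Episode length is assumed, nothing in the documents suggests that it differs between arms, and unremitted patients push the count up.

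**Conclusion.** The point holds for the definition in Methods/design. As stated there, relapse is status at one visit. It misses episodes that resolve before the visit and counts patients who never improved. The second definition, in Secondary outcomes, is not reconciled with the first, and the article does not say which one tests the secondary hypothesis.

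The size is conditional. If all patients are well at end of treatment, the hazard is constant at 29 % per year and episodes are exponential, 22 % to 58 % of relapses by 6 months would be missed for mean episodes of 12 down to 3 months. The net error in the relapse rate cannot be signed from the documents, because the number of unremitted patients is unknown. Whether the interview shares the first weakness is open.

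The primary outcome is unaffected. The matter should be settled before the relapse data are analysed, because it determines what the secondary hypothesis means.

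**What to change.** 1. Reconcile Methods/design and Secondary outcomes to one definition for the secondary hypothesis: DSM-IV criteria for a depressive episode met at any time between end of treatment and the 6-month visit.
2. State that the blinded interview already planned covers the whole interval and records the month of onset.
3. State how patients not remitted at end of treatment are handled. One option is to report relapse among those below the HRSD cut-off at end of treatment alongside the result for all randomised patients. The first set is defined after randomisation, so its comparison should be read with that in mind.
4. Report HRSD of 13 or more at 6 months separately, labelled as current depression.

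The cost is a wording change and a few more minutes in an interview already scheduled, with no extra visit, staff or patients. The downside is modest recall error over 6 months, collected in the same way in both arms by blinded assessors. Recruitment was ongoing when the article was written, so later follow-ups can use the change. Patients already seen should not be back-filled from case records: those notes are unblinded, and the article does not show that they cover the 6 months after treatment.

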### Adverse events

All adverse events will be monitored by the psychotherapists and the psychiatrists at the outpatient service and reported in the patient case report. If a patient is at risk of an adverse event, a psychotherapist, psychiatrist, or research staff will take immediate action to prevent any adverse event from happening. Use of anti-depressive medication will be administered and monitored by experienced psychiatrists at the outpatient service. There are no study-specific restrictions on change of dosage of or types of anti-depressant medications. Medications, adverse effects due to medication, and changes in medical treatment will be reported in the patient case record by the psychiatrists. We will compare the levels of usage of anti-depressant medication and the reported adverse effects across the arms by conducting a screening of the participants’ case reports when all participants have finished treatment.

## Statistical considerations

### Sample size estimation

Assuming similar mean changes in HRSD scores from pre- to post-intervention as found by Watkins and colleagues [18] for RFCBT (M = 7.81) and by Paykel and colleagues [11] for CBT (M = 3.52) and a conservative estimate of pooled standard deviation for change in HRSD of 6 (when standard deviation = 3.60 for change in HRSD in RFCBT), we estimate a between-treatment effect size of Cohen’s *d* = 0.7. To detect a difference in effect size of 0.7 between g-RFCBT and g-CBT at a two-tailed significance level of 5 %, each treatment arm requires 44 patients to obtain 90 % statistical power [40]. Assuming a dropout rate of 20 %, we will recruit 55 patients into each treatment arm. With an average size of the therapy group of *m* = 8 in both treatment arms and an intraclass correlation of about *ρ* = 0.05, a design effect of 1 + (*m* – 1)*ρ* = 1.35 follows, so that we plan to recruit eight groups in each treatment arm (128 patients in total).

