### Recruitment

The study takes place in a community psychiatric outpatient service in Hillerød, Denmark, which treats 200–250 patients with diagnosed depression per year. Patients who are referred for treatment with a primary diagnosis of depression, recurrent or chronic, will be recruited to the study. We plan to recruit a total of 128 patients, 64 in each treatment arm.

The psychiatrist conducting the initial evaluation of the patients will invite the patients to talk to the researcher if the inclusion criteria are met. Written informed consent will be obtained from all patients prior to enrolment in the study. The researcher will validate the depression diagnosis and screen for DSM-IV Axis I co-morbidity by using the structured International Neuropsychiatric Interview M.I.N.I. version 5.0 [23] and for DSM-IV Axis II disorders by using the Standardized Assessment of Personality-Abbreviated Scale, an eight-item semi-structured interview screening for the presence of a personality disorder [24]. Patients meeting the inclusion criteria will be included in the study, and baseline assessment will be conducted within 2 weeks prior to commencement of the psychotherapeutic treatment. After the baseline assessment, the patients are randomly assigned to receive one of the two treatment options.

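### The 128-patient target does not follow from the stated 20 % dropout and design effect of 1.35 taken together; on the calculation shown it gives about 85 % power, not the implied 90 %

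*Protocol article*

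**What the plan says.** All the steps stand in one paragraph of the protocol article, under Statistical considerations, Sample size estimation:

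- **Effect size.** Mean changes of 7.81 and 3.52 points on the HRSD, with "a conservative estimate of pooled standard deviation for change in HRSD of 6", are taken as d = 0.7.
- **Base size.** "To detect a difference in effect size of 0.7 between g-RFCBT and g-CBT" at the two-sided 5 % level, "each treatment arm requires 44 patients to obtain 90 % statistical power".
- **Dropout.** "Assuming a dropout rate of 20 %, we will recruit 55 patients into each treatment arm".
- **Clustering.** "With an average size of the therapy group of *m* = 8 in both treatment arms" and an intraclass correlation of about 0.05, the design effect is given as 1.35.
- **Conclusion.** "so that we plan to recruit eight groups in each treatment arm (128 patients in total".

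The Recruitment section repeats the target: "We plan to recruit a total of 128 patients, 64 in each treatment arm". No power is stated for 128. The only power figure is the 90 % attached to 44 per arm.

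**The concern.** The paragraph reads as a chain in which each step builds on the one before, and its last link presents the target as the result of the design effect. The step from 55 to 64 per arm is a factor of 64 / 55 = 1.16, where the stated design effect is 1.35. One of the two inflations is therefore not fully applied, and the text does not say that one replaces the other.

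The calculation concerns the primary outcome of a trial that describes itself as the first direct comparison of the two therapies. A reader will take 128 as giving 90 % power after dropout and clustering. If the result is not significant, it will be judged against a power that the stated assumptions do not give.

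**Working it through.** **Inputs, all from the sample size section:** two-sided α = 0.05; d = 0.7; 44 per arm for 90 % power; dropout 20 %; group size m = 8; ρ = 0.05; target 64 per arm. Power is from the two-sample t test (noncentral t, df = 2n − 2, where n is the effective number per arm).

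**1. The plan's intermediate figures reproduce.**
- d = (7.81 − 3.52) / 6 = 0.715, stated as 0.7.
- For d = 0.7 and 90 % power, n = 43.87, so 44 per arm (power 90.1 %).
- 44 / (1 − 0.20) = 55 per arm.
- Design effect = 1 + (8 − 1) × 0.05 = 1.35.

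**2. The final figure does not.**
- Both inflations: 44 × 1.35 / 0.8 = 55 × 1.35 = 74.25, so 75 per arm (150 in total).
- Clustering only: 44 × 1.35 = 59.4 per arm, which is 7.4 groups of 8. Rounded up, this is 8 groups, or 64 per arm. This is a route that leads to the plan's figure, and it leaves dropout out.
- Dropout only: 55 per arm.
- Taking dropout as a 20 % addition instead: 44 × 1.2 × 1.35 = 71.3, still above 64.

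**3. Power that 64 per arm gives on this calculation, d = 0.7.**

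| Group size in the design effect | Design effect | Effective n per arm | Power | d for 90 % power |
|---|---|---|---|---|
| 8, as stated | 1.35 | 64 × 0.8 / 1.35 = 37.9 | 85.3 % | 0.75 |
| 6.4 (8 × 0.8, after dropout) | 1.27 | 64 × 0.8 / 1.27 = 40.3 | 87.4 % | 0.73 |

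With the unrounded d = 0.715, the two powers are 86.7 % and 88.7 %. Even the most favourable of these combinations stays below 90 %.

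**4. Size of the gap in groups.** 74.25 / 8 = 9.28 groups per arm. Nine groups (72 per arm) give 72 × 0.8 / 1.35 = 42.7 effective patients and 89.2 % power, or 90.9 % with the design effect of 1.27. Ten groups (80 per arm) give 92.1 % with 1.35. The gap is thus between one and two therapy groups per arm, and closer to one.

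**5. What the planned baseline adjustment could add.** The Data analysis section adjusts for baseline HRSD, while the sample size uses the SD of change. With equal variances at both visits and baseline–post correlation r, the change-score variance is 2σ²(1 − r) and the adjusted residual variance is σ²(1 − r²). Their ratio is (1 + r) / 2, so the working effect becomes 0.7 / √((1 + r) / 2). The documents give no r; the values below are assumptions, at 37.9 effective patients per arm:

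| r (assumed) | Working d | Power |
|---|---|---|
| 0.3 | 0.868 | 96 % |
| 0.5 | 0.808 | 93 % |
| 0.7 | 0.759 | 90.4 % |

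Power falls below 90 % above r of about 0.72.

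**6. Sensitivity to the reference distribution.** If the arm effect were tested with 14 degrees of freedom (16 therapy groups − 2), the unadjusted power in step 3 would be 80.9 % with the design effect of 1.35. The article names no degrees-of-freedom method, so this is a sensitivity figure only.

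**The case against.** The strongest reply is that the planned test is not the one used for the sample size. It adjusts for baseline, and under equal variances its residual SD cannot exceed the SD of change. At correlations up to about 0.7, the same 128 patients would then have 90 % power or more. This stands as far as it goes: a reader might infer that the design lacks 90 % power, or can reach it only with a smaller intraclass correlation or less dropout, and the documents do not support either inference. It does not rescue the written derivation, which uses a change-score SD, states no correlation and claims no gain from the covariate.

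Three further points:

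- **The 90 % belongs to 44 per arm and is never restated for 128.** This is correct. The 90 % for 128 is implied by the chain of steps, not stated.
- **Multiple imputation keeps all randomised patients in the analysis.** This carries little weight here. The plan itself inflates for dropout, so it does not count on imputation to restore the lost information.
- **The low figure of about 81 % should not be used.** A reader might infer from the random-intercept model that the test has only 14 degrees of freedom. The article does not say so, and such detail is commonly left to the analysis plan. The figure is no part of the conclusion.

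**Conclusion.** The point holds as an error in the written derivation. The stated inputs lead to 75 per arm, not 64, and no other section repairs this. On the unadjusted calculation shown, with d = 0.7, 20 % dropout and ρ = 0.05, the target of 128 gives about 85 % power, or about 87 % if the design effect is computed on groups of 6.4. That is about 3 to 5 percentage points below the implied 90 %.

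The severity is moderate. Power stays above 80 %, and the hypothesis, significance level and analysis model are untouched. Whether the planned baseline-adjusted test reaches 90 % with 128 patients cannot be settled from the article, because it depends on a correlation that is not given.

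**What to change.** Keep 128 and amend the end of the sample size paragraph in one of two ways:

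1. State what the target gives, for example: 64 patients per arm give about 85 % power (85–87 %, depending on whether group size is taken before or after dropout) for d = 0.7 after 20 % dropout and clustering with an intraclass correlation of 0.05; 90 % power is reached at d of about 0.75 (0.73 with the smaller groups).
2. Or justify 90 % from the planned baseline-adjusted model, and state the assumed baseline–post correlation with its source. With equal variances and ordinary t degrees of freedom, any value up to about 0.7 suffices. If the analysis will use a small-sample degrees-of-freedom method, the power should be computed with that method.

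Either way, the text should say how the dropout and clustering allowances combine. The cost is one or two sentences and no extra patients. Under the first option the stated power becomes less favourable.
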